## Abstract

**Introduction:**

Dietary zinc (Zn) deficiency is a global problem, particularly in low-income and middle-income countries where access to rich, animal-source foods of Zn is limited due to poverty. In Pakistan, Zn deficiency affects over 40% of the adult female population, resulting in suboptimal immune status and increased likelihood of complications during pregnancy.

**Methods and analysis:**

We are conducting a double-blind, randomised controlled feeding study with cross-over design in a low-resource setting in Pakistan. Households were provided with flour milled from genetically and agronomically biofortified grain (Zincol-2016/NR-421) or control grain (Galaxy-2013). Fifty households were recruited. Each household included a woman aged 16–49 years who is neither pregnant nor breastfeeding, and not currently consuming nutritional supplements. These women were the primary study participants. All households were provided with control flour for an initial 2-week baseline period, followed by an 8-week intervention period where 25 households receive biofortified flour (group A) and 25 households receive control flour (group B). After this 8-week period, groups A and B crossed over, receiving control and biofortified flour respectively for 8 weeks. Tissue (blood, hair and nails) have been collected from the women at five time points: baseline, middle and end of period 1, and middle and end of period 2.

**Ethics and dissemination:**

Ethical approval was granted from the lead university (reference no. STEMH 697 FR) and the collaborating institution in Pakistan. The final study methods (including any modifications) will be published in peer-reviewed journals, alongside the study outcomes on completion of the data analysis. In addition, findings will be disseminated to the scientific community via conference presentations and abstracts and communicated to the study participants through the village elders at an appropriate community forum.

**Registration details:**

The trial has been registered with the ISRCTN registry, study ID ISRCTN83678069.

Strengths and limitations of the studyThe study is the first randomised controlled trial to determine the effectiveness of consuming flour from the Zincol-2016/NR-421 strain of wheat on Zn status in women of childbearing age.The study will evaluate the use of novel biomarkers of Zn status in low-resource settings.A limitation of this study is the relatively small sample size (n=50). This is compensated for by the cross-over design, which strengthens the statistical power.

## Introduction

Dietary zinc (Zn) deficiency is a global problem, affecting 17% of the world’s population, with the greatest burden in low-income and middle-income countries.^1 2^ The most recent national survey in Pakistan indicates that over 40% of women are Zn deficient.^3^ The consequences of Zn deficiency are profound and far-reaching, ranging from increased individual morbidity and mortality to problems with community and regional economic development.^4^

Attempts to alleviate the problem of Zn deficiency, both in Pakistan and in other countries, have followed several strategies. Providing micronutrient supplements, usually using ‘sprinkles’, has been attempted under different circumstances, generally with some success.^5^ However, it is an expensive and intensive approach, and without close supervision it can often be that the intended target, for example a pregnant woman, does not end up receiving the supplement. Fortification of foods at the processing stage has also been widely adopted, but there are significant problems with compliance and efficacy, both at the fortification stage where quality control is ineffective and at the level of consumer uptake. A major issue is that poorer households in rural areas of developing countries typically grow the majority of their food and process it at village or community level. Thus, cereal fortification at large-scale processing facilities may not reach poorer households, where micronutrient deficiencies are often more prevalent and severe.

An alternative approach is to intervene at agricultural production stage through biofortification to achieve greater concentrations of bioavailable vitamins or elements in the edible portion of crops.^6^ Biofortification can be realised through crop breeding or application of element-enriched fertilisers, known as ‘agronomic biofortification’, which is particularly important in Pakistan where plant-available soil Zn concentrations are low.^7^ Such Zn-deficient soils that constitute 52% at national scale are also prevalent in Peshawar, Khyber Pakhtunkhwa Province, where plant-available soil Zn concentrations are significantly below the threshold 1 mg/kg in 75% of the soils analysed. Farmers in Pakistan rarely apply Zn fertilisers to their crops except for rice. Biofortification approaches have focused on staple crops because they are widely consumed including households with low purchasing power. Recently, varieties of maize, pearl millet and beans with high iron (Fe) and Zn concentrations have been developed by the HarvestPlus programme for deployment in low-income settings. Human feeding studies have demonstrated that such varieties can lead to improvements in Fe and Zn intake and status,^8 9^ although there may be issues with low bioavailability.^10^ Agronomic biofortification has not previously been deployed in a low-income setting but does have policy precedent in Finland, where granular fertilisers were enriched with selenium (Se) since the mid-1980s with consequent increases in human dietary Se intakes and eventual elimination of Se deficiency as a public health problem.^11^

Preliminary studies have shown that Zn concentrations in wheat can be raised substantially through biofortification strategies.^12^ It is notable that increasing levels of nutrients in the whole plant is not sufficient; elements must be translocated to the edible component of the grain (endosperm) and must be bioavailable. Phytic acid (PA) is the most important inhibitor of Zn absorption from wheat; therefore, the Zn:PA molar ratio of the endosperm is an important consideration. The process of element accumulation in the endosperm is not simple. For example, Zn moves through many different transport processes prior to being deposited in the seed.^13^ In a recent set of experiments within the HarvestPlus programme over a period of 8 years, scientists in Pakistan using traditional breeding techniques have been able to generate a ‘high Zn’ variety of wheat that is adapted to Pakistan conditions. The variety (Zincol-2016/NR-421) contains more Zn per kilogram of grain compared with traditional varieties. However, grain Zn concentration will also depend on the availability of Zn in the soil, and there are likely to be synergistic effects of breeding for high Zn with application of Zn fertilisers.

The efficacy of increasing dietary intake through biofortification on individual and population Zn status is notoriously difficult to measure. The assessment of Zn status has been the subject of considerable research and is summarised comprehensively in two recent reviews supported by multinational expert groups.^14 15^ Both reviews conclude that plasma or serum Zn concentration, the most widely used biomarker, is useful provided that various confounding factors are considered (including concurrent infection and inflammation). However, the plasma/serum must be collected following stringent methodology to avoid contamination and can be difficult to achieve in field settings. Hair Zn concentration is also potentially useful, and samples are easy to collect and store. In addition, emerging techniques, including the measurement of DNA fragmentation using the Comet assay and analysis of nail Zn concentration using laser ablation, are gaining credibility as useful biomarkers of Zn status. However, field trials are needed to evaluate their usefulness.

The primary aim of this study is to measure the impact of consuming flour made from the recently released high-Zn wheat grain variety Zincol-2016/NR-421 on dietary Zn intake and biomarkers of Zn status in a low-resource rural community setting in Pakistan. The secondary aim is to evaluate the potential usefulness of new biomarkers of Zn status. These aims will be achieved through conducting a randomised controlled feeding study with a cross-over design. Comparison of outcome measures will be made following consumption of flour made from the biofortified wheat variety, Zincol-2016/NR-421, and the control, non-biofortified variety, Galaxy. The trial has been registered with the ISRCTN registry, study ID ISRCTN83678069.^16^

## Methods and analysis

### Study setting and recruitment

This study was conducted from the Health Centre that serves a community of approximately 5000 households in an area of 8 km^2^ on the outskirts of Peshawar in Khyber Pakhtunkhwa (KPK). This community was chosen because previous studies have indicated that Zn deficiency is widespread, the diet is limited and primarily vegetable-based (thus low in bioavailable Zn) and the staple is wheat which is used for making chapati and roti.^17^ The catchment area, known as a Union Council, is made up of 10 villages (clusters). Out of 10 clusters in the union council, 5 were randomly selected, from which equal numbers of households were randomly selected for the study. Selection of these clusters and households into intervention or control arm was done using a block design. Water samples were collected in duplicate from four different communal tube wells (hand pump) supplying each village and analysed for mineral content by inductively coupled plasma-mass spectrometry (ICP-MS). The mean Zn concentration of the water from one cluster was high enough to significantly impact on daily Zn intake (>250 µg/L); therefore, this cluster was eliminated from the study and an alternative cluster was randomly selected. The mean Zn concentration in the water analysed from the five included clusters was ≤120 µg/L and therefore not considered to add significantly to the daily Zn intake, based on a consumption of 2–4 L water per day (<0.5 mg Zn per day).

Ten households from each cluster were randomly selected. The head of the household was approached, the purpose of the study explained and, if eligible, the family invited to participate in the trial. If the head of the household declined, another house from the cluster was randomly selected and the invitation process repeated. Inclusion criteria were the household included a woman aged 16–49 years who was neither pregnant nor breastfeeding, and not currently consuming nutritional supplements. When there was more than one eligible woman in the household, one was conveniently selected with agreement from the head of the household. There were no additional exclusion criteria. Following informed consent, each household was assigned to treatment arm A or B (refer to figure 1) using a block design. A sample size of 40, 95% significance level (two-sided) and 90% power, will enable an increase in plasma Zn concentration of 3.1 µg/dL to be detected. The target was to recruit 50 households (50 eligible women) to be able to accommodate a 20% attrition rate during the 18-week study. The project manager led the recruitment process because he is known to the community through previous health-related projects associated with the Abaseen Foundation PK (AFPK), a local non-governmental organisation and key member of this project team, along with its sister organisation Abaseen Foundation UK. There is a high level of trust and cooperation between community members and the AFPK who operate the health centre that serves this Union Council; therefore, high levels of participant enrolment has been achieved. The project manager was responsible for allocating participants to each arm of the cross-over trial using a block design. Only the project manager had access to this information.

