**Figure 1 F1:**
[figure not shown]
Schematic overview of objective 1, randomised controlled feeding study with cross-over design.

The participants and the remaining research team members, including the PI and Co-Is, database manager and data analysts were blind to the order in which households received the biofortified or control flour. Unblinding was permissible if any adverse reactions are reported by the households during the trial.

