## Data collection and storage

Sample analysis will take place in a number of different specialist laboratories in the UK (University of Nottingham: plasma Zn, Fe and SE, water, flour), USA (NeurobioTex: nail and hair Zn concentration) and Pakistan (KMU: Comet assay, haematology, serum transferring receptor, ferritin, RBP and inflammatory markers). Comet assay tail-moment analysis will be undertaken by both Pakistan-based (KMU) and UK-based (University of Central Lancashire, UCLan) teams, and the results compared. Any significant differences will be resolved with expert support from the Children’s Hospital Oakland Research Institute. Sample analysis will be undertaken in duplicate as a minimum requirement. Data entry will be undertaken by the expert laboratory and encrypted spreadsheets sent to the data hub where a final check for anomalies will be made by the database manager. Any potential anomalies identified will be checked with the expert laboratory. All data will be managed compliant with standard BBSRC policies (http://www.bbsrc.ac.uk/web/FILES/Policies/data-sharing-policy.pdf). The UCLan will be the data hub for the project; UCLan adheres to an Open Data policy and has an open data repository. Metadata will be collected in the form of ‘read me’ files using basic Dublin Core. This study will generate small quantities of personal data from the analysis of blood and hair/nail samples. Most of the participants were illiterate so verbal informed consent was obtained and recorded by the project manager. Participants were given an ID number on recruitment, and this will be used in all data files. The list of names associated with the ID numbers is known only by the project manager and is stored in a locked filing cabinet. Data collected in the field on laptops are password protected. UCLan systems are automatically backed up. Transfer of data between laboratories will be in the form of encrypted Excel or Word files. Data and metadata will be securely stored in a project database and reported on publication. Data will be shared with the project steering committee during the bi-monthly meetings. This committee is composed of the PI and Co-Is. The database manager is undertaking the role of data monitoring and all members will have access to the final database.

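### Concealment of allocation from the recruiter is not secured: one person recruits, takes consent, allocates and holds the allocation, while the measured woman may be picked by convenience

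*Protocol article*

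**What the plan says.** All statements are in the Protocol article.

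- **Recruitment** (Study setting and recruitment): "The project manager led the recruitment process because he is known to the community through previous health-related projects".
- **Consent** (Data collection and storage): "verbal informed consent was obtained and recorded by the project manager".
- **Allocation** (Study setting and recruitment): "The project manager was responsible for allocating participants to each arm of the cross-over trial using a block design". No block size is given.
- **Custody of the allocation** (same section): "Only the project manager had access to this information".
- **Blinding** (paragraph under Figure 1): "The participants and the remaining research team members, including the PI and Co-Is, database manager and data analysts were blind". The word for the rest of the team leaves the project manager, by implication, unblinded.
- **Choice of the measured woman** (Study setting and recruitment): "When there was more than one eligible woman in the household, one was conveniently selected with agreement from the head of the household". Who made the choice is not stated.
- **Order of steps** (same section): "Following informed consent, each household was assigned to treatment arm A or B".

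Villages and households, including replacements for those that declined, were drawn at random. Under Comparisons between groups A and B, the primary question is answered by unpaired tests of A against B at weeks 8 and 16. Linear mixed modelling is named there for the adjusted analyses.

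**The concern.** Concealment protects a trial only if the person who enrols participants cannot foresee the next assignment. Here enrolment, consent, assignment and custody of the allocation rest with one person, and no separation of these roles is described. Random sampling of households limits selection at that level. The last step, which woman in the household is measured, is left to convenience when several are eligible.

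If the coming arm can be known or predicted at that step, the age, health or Zn status of the chosen women could differ between groups A and B. Blinding laboratories and analysts afterwards does not undo a difference created at entry. At stake is the comparability of the two groups in the unpaired tests that carry the primary question.

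**Working it through.** The plan gives no figure on this point to reproduce. The check has three parts.

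**1. Roles and order.** Set side by side, the statements put recruitment, consent, block allocation and sole access with the project manager. Assignment comes after consent. The text does not say whether the woman was chosen before consent, whether a list existed beforehand, or whether households were assigned one by one. Earlier in the same section, the selection of clusters and households and their placement in an arm are described together as one block-design step, which leaves the order less clear.

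**2. How predictable a block design is to the person running it.** Block size *b* is an assumption, because none is stated. For 1:1 permuted blocks, and a person who knows *b* and the past assignments:

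- expected share of correct guesses = 1/2 + [2^b / C(b, b/2) − 1] / (2b)
- share of assignments that are certain in advance = 1 / (b/2 + 1)

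| b | correct guesses | certain in advance |
|---|---|---|
| 2 | 1/2 + (4/2 − 1)/4 = 75% | 1/2 = 50% |
| 4 | 1/2 + (16/6 − 1)/8 = 71% | 1/3 = 33% |
| 6 | 1/2 + (64/20 − 1)/12 = 68% | 1/4 = 25% |
| 10 | 1/2 + (1024/252 − 1)/20 = 65% | 1/6 = 17% |

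Chance is 50%. A block of 10 would correspond to one block per cluster (five clusters of ten households). Of 50 households, the assignment would be certain in advance for 25 with blocks of 2 and for about 8 with blocks of 10. With a list prepared beforehand and held by the recruiter, every assignment would be known. If a whole cluster was enrolled before any of its households was assigned, nothing could be predicted.

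**3. What a difference between the women does to the analysis.** Let *τ* be the effect of biofortified against control flour and *d* a stable A-minus-B difference between the women. Ignore carry-over.

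- Week 8, A on biofortified flour: A − B = τ + d.
- Week 16, B on biofortified flour: B − A = τ − d.
- Within-woman contrast, with *π* the period-2-minus-period-1 shift: group A gives τ − π and group B gives τ + π. Their average is τ, and *d* has cancelled.

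So *d* enters each unpaired test in full, but with opposite sign. The comparisons listed under Within-group (A and B) comparisons include none across the cross-over, so they do not supply the contrast in which *d* cancels.

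**Illustration of size, on assumptions only.** Suppose 30–60% of households had more than one eligible woman (0.30 × 50 = 15 to 0.60 × 50 = 30 households), and that choice produced a 3 µg/dL difference between groups among those women. Then d = 0.30 × 3 = 0.9 to 0.60 × 3 = 1.8 µg/dL, against the 3.1 µg/dL the trial is sized to detect. Neither assumption has support in the article. The average household of seven includes children, and pregnant, breastfeeding and supplement-taking women are not eligible. Unsteered choice would give much less.

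**The case against.** The strongest reply is that the stated order protects the trial. The household is drawn at random, eligibility is checked, consent is taken, and only then is the household assigned. If the woman was chosen before consent and the assignment was then drawn afresh, convenience selection affects representativeness and not balance. The choice also needed the agreement of the household head, and the households were blind. Sole access may simply mean knowledge held after assignment. Block size and sequence mechanics are details that an article commonly leaves to the full protocol.

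Much of this stands. A reader might infer that allocation was not concealed, or that the woman was picked with the arm in view. The documents support neither: they do not say who chose her, how large the blocks were or whether a list existed, and they put assignment after consent. A reader might also infer that differences between the women pass straight into the result in favour of biofortified flour. That is too strong: a stable difference reverses sign between the two periods, so a discrepancy between weeks 8 and 16 could reveal it, and the planned mixed model takes account of baseline.

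What the reply does not remove is the arrangement of roles, which the article states and does not merely leave out. Placing assignment after consent does not secure concealment when the person taking consent also runs the blocks.

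**Conclusion.** Concealment of allocation from the recruiter is not secured, and the convenience choice of woman opens a route for selection bias. No actual bias is shown.

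The role structure and the absence of a selection rule rest on the text alone. The size does not. Predictability of 65–75% against 50% by chance assumes blocks of 10 down to 2, assignment one household at a time, and a recruiter who knows the block size. The route operates only in households with more than one eligible woman, whose number is not given. The consequence is greatest for the unpaired A-versus-B tests and largely disappears in a within-woman contrast. With recruitment complete, the usable remedy is mainly one of reporting and analysis.

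**What to change.** **For any further recruitment.** Choose the woman by a chance rule from the list of eligible women in the household and register her before assignment. Have an existing partner outside recruitment hold the sequence and release each assignment only after consent and selection are recorded. This costs one line of procedure and a change in who keeps the list.

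**For the households already enrolled.**

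- Report the order in which the woman was chosen, consent taken and the household assigned, and the block size.
- Tabulate baseline values by group, and the number of eligible women per household if it was recorded. All households receive control flour in the baseline period, so flour type does not confound this check.
- Rest the primary inference on the baseline-adjusted, within-woman mixed-model contrast of biofortified against control periods in place of the unpaired tests. Mixed modelling is already planned; the cost is to state this contrast as primary before the allocation is unblinded.
- If the counts exist, repeat the analysis in households with one eligible woman as a sensitivity check only. On the assumed 30–60% share this leaves 50 − 30 = 20 to 50 − 15 = 35 households, below the 40 that the sample size requires, so power would be low.

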**Figure 1 F1:**
[figure not shown]
Schematic overview of objective 1, randomised controlled feeding study with cross-over design.

The participants and the remaining research team members, including the PI and Co-Is, database manager and data analysts were blind to the order in which households received the biofortified or control flour. Unblinding was permissible if any adverse reactions are reported by the households during the trial.

